### Outcomes

The primary outcome for the first aim will be the performance of the AIm-PBC disease activity index compared to conventional monitoring strategies. This will be assessed through its calibration against established risk scores such as UK-PBC and GLOBE [22,23], as well as its responsiveness to clinically meaningful changes in disease activity. The ability of the integrated symptom indexes to correlate with biochemical progression or regression will also be evaluated, providing insights into whether the inclusion of PROs enhances the sensitivity of disease monitoring. Explainability will be measured via the interpretability of SHAP-based visualizations and their perceived clinical utility during clinician evaluations.

For the second aim, the primary outcome will be the discriminatory ability of the multi-signal predictive model to identify patients at high risk of CSPH and early complications such as variceal hemorrhage or ascites. This will be quantified using the area under the receiver operating characteristic curve (AUROC), with additional measures of calibration and clinical utility assessed through decision curve analysis and net reclassification improvement. Comparative analyses will determine whether the composite model outperforms single-modality rules and consensus criteria such as Baveno VII, and subgroup analyses will explore performance consistency across patients with AIH overlap and MASH.

For the third aim, the primary outcome will be the effectiveness and usability of the EHR-integrated CDS prototype. Effectiveness will be measured via improvements in clinician adherence to guideline-concordant care pathways, including pruritus management, bone health interventions, and risk-based endoscopy referrals. Usability will be assessed using the System Usability Scale, with a target score of 70 or higher, and cognitive load will be evaluated using the NASA-Task Load Index. Clinician trust in the AI system will be measured through the AI trust scale, whereas decision accuracy and decision time will be compared between CDS-assisted and usual care conditions during the randomized crossover simulation. Feasibility indicators, including recruitment and completion rates, will be monitored during the pragmatic pilot phase.

Secondary outcomes will include fairness metrics to ensure equitable model performance across demographic and clinical subgroups, defined as an AUROC parity gap of no more than 5%. Additional exploratory outcomes will examine the impact of the intervention on workflow efficiency and clinician confidence in decision-making.

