### Interventions

The intervention consists of the development and deployment of the AIm-PBC framework across 3 sequential phases. The first phase focuses on building an agentic AI system capable of continuous monitoring of disease activity and symptom burden. This system will integrate multiple data streams, including monthly biochemical markers, periodic elastography measurements such as LSM and SSM, and high-frequency PROs collected through validated instruments such as the WI-NRS and the PBC-40. The agent will autonomously orchestrate data ingestion, normalization, and analysis to generate an explainable disease activity index supported by SHAP-based visualizations to ensure interpretability for clinicians.

The second phase involves the creation and validation of a multi-signal predictive model for early identification of portal hypertension complications. This model will combine elastography metrics, platelet count, biochemical response trajectories, and comorbidity profiles, including AIH and MASH overlap. By leveraging gradient-boosted ensemble algorithms and explainability frameworks, the model aims to outperform existing single-modality rules and consensus criteria such as Baveno VII [24], providing a noninvasive, accurate method for triaging endoscopy referrals and initiating prophylactic interventions.

The third phase operationalizes these insights through an EHR-integrated CDS prototype. Built within a SMART-on-FHIR architecture, the CDS tool will present clinicians with interpretable risk cards; dual-threshold triage cues; and guideline-based order sets for interventions such as pruritus step therapy, bone health management, and endoscopy referral. This phase includes a randomized crossover simulation to evaluate usability, decision accuracy, and cognitive load, followed by a pragmatic pilot in hepatology clinics to assess feasibility and effectiveness in real-world workflows. Collectively, these interventions aim to transform PBC care by embedding explainable AI into routine practice, improving monitoring, risk prediction, and adherence to evidence-based management strategies.

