### Statistical Analysis

For the first aim, longitudinal PROs and biochemical markers will be analyzed using mixed-effects models to account for within-subject correlation and repeated measures over time. These models will assess the responsiveness of integrated symptom indexes to changes in biochemical progression or regression, whereas calibration of the AIm-PBC disease activity index will be evaluated against established risk scores such as UK-PBC and GLOBE using the calibration slope, intercept, and Brier score. Discrimination will be quantified through the AUROC, and visualizations of SHAP values will be examined to confirm clinical interpretability.

For the second aim, the predictive model for CSPH complications will be developed using gradient-boosted ensemble algorithms chosen for their robustness in handling heterogeneous data. Model performance will be assessed through the AUROC for discrimination and calibration plots for agreement between predicted and observed outcomes. Clinical utility will be evaluated using decision curve analysis and net reclassification improvement to determine whether the composite model offers meaningful improvement over existing criteria. Comparative analyses will use DeLong tests to assess differences in AUROC between models, and subgroup analyses will be conducted to evaluate fairness and consistency across patients with AIH overlap and MASH. Ablation studies will quantify the incremental value of individual predictors, particularly SSM, by systematically removing variables and observing changes in performance.

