For the third aim, implementation outcomes will be analyzed using both descriptive and inferential methods. Usability scores from the System Usability Scale (Multimedia Appendix 1), clinician trust scores from the AI trust scale adapted for AIm-PBC (Multimedia Appendix 2), and cognitive load measures from the National Aeronautics and Space Administration Task Load Index (Multimedia Appendix 3) will be summarized and compared between CDS-assisted and usual care conditions. Decision accuracy and decision time will be analyzed using 2-tailed paired *t* tests within the randomized crossover simulation, whereas clinician adherence to guideline-concordant care pathways will be evaluated using within-clinician comparisons across study phases. Feasibility indicators, such as recruitment and completion rates, will be reported as proportions with CIs. Qualitative debriefing interviews will be analyzed to explore clinician perceptions of usability, workflow integration, trust, and barriers to implementation (Multimedia Appendix 4). Fairness metrics, including AUROC parity gaps across demographic and clinical subgroups, will be calculated to ensure equitable performance of the CDS tool.

All analyses will be conducted using validated statistical software packages in R (R Foundation for Statistical Computing) and Python (Python Software Foundation), with significance thresholds set at a 2-sided α value of .05. Missing data will be addressed through multiple imputation techniques, and sensitivity analyses will be performed to confirm the robustness of the findings.

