## Results

At the time of manuscript submission, this protocol had not yet begun participant recruitment or data analysis. No participants had been recruited. The study did not receive external funding; therefore, no funding date is applicable. Data collection is projected to begin after institutional review board approval and ClinicalTrials.gov registration, with retrospective data extraction and prospective observational data collection expected to occur over approximately 24 months. The clinician-level randomized crossover simulation and pragmatic pilot implementation phases are expected to occur after model development and validation are completed. Data analysis will begin after completion of the relevant data collection phases. The main study findings are expected to be submitted for publication in summer 2029.

The integrated disease activity index is expected to show strong calibration with established prognostic scores and greater responsiveness to clinically meaningful changes, whereas the inclusion of PROs will provide a more comprehensive view of symptom burden. The predictive model is expected to achieve an AUROC of at least 0.85 for identifying CSPH and deliver a net reclassification improvement of 10% or more over Baveno VII criteria, reducing unnecessary endoscopies without compromising safety. Finally, the CDS prototype is expected to improve clinician adherence to guideline-concordant care pathways, reduce decision time, and achieve high usability and trust scores during the simulation and pilot phases.

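### Equity is defined only by a between-group AUROC gap, which a model can satisfy while under- or over-predicting CSPH risk in one subgroup

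*Protocol article*

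**What the plan says.** In Outcomes, the secondary outcome is "fairness metrics to ensure equitable model performance across demographic and clinical subgroups, defined as an AUROC parity gap of no more than 5" percent. This is the only numerical rule for equity in the document. The third-aim part of Statistical Analysis repeats it: "Fairness metrics, including AUROC parity gaps across demographic and clinical subgroups, will be calculated to ensure equitable performance of the CDS tool".

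Interventions describes what the tool shows clinicians: "interpretable risk cards; dual-threshold triage cues; and guideline-based order sets for interventions such as pruritus step therapy, bone health management, and endoscopy referral". The CSPH model behind it is meant as "providing a noninvasive, accurate method for triaging endoscopy referrals and initiating prophylactic interventions".

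Calibration of that model is planned in the second-aim part of Statistical Analysis: "Model performance will be assessed through the AUROC for discrimination and calibration plots for agreement between predicted and observed outcomes". The same paragraph adds that "subgroup analyses will be conducted to evaluate fairness and consistency across patients with AIH overlap and MASH", without naming the measure to be used. Nowhere is calibration specified by subgroup or made part of what counts as equitable.

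**The concern.** AUROC within a subgroup is the probability that a randomly chosen patient with CSPH in that subgroup scores higher than a randomly chosen patient without it. It depends only on the order of the scores. If predicted risk is too low or too high throughout a subgroup but the order is kept, that subgroup's AUROC does not change.

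A triage cue depends on where the predicted risk lies relative to a threshold. Under-prediction in one subgroup moves its CSPH patients below a threshold that similar patients elsewhere would exceed. The criterion is thus set on a different scale from the decision it is meant to protect. Sampling error is not the cause, so a larger cohort would not remove the problem. What is at stake is the equity claim: meeting the stated rule would not support it.

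**Working it through.** **Inputs from the protocol**
- AUROC 0.85, from Results: "The predictive model is expected to achieve an AUROC of at least 0.85 for identifying CSPH".
- CSPH prevalence 24% to 47% and N = 600, from Sample Size and Power Considerations. The stated event counts reproduce: 600 × 0.24 = 144 and 600 × 0.47 = 282. The 5% mark has no derivation to reproduce.

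**Assumptions, because the document gives no values**
- Score normally distributed with equal variance in patients with and without CSPH.
- Model calibrated in group A; predicted odds in group B are half the true odds.
- The same risk cut-off t in both groups, varied from 10% to 50%. These cut-offs are illustrative only and are not proposals.

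**Formulas**
- Separation: d = √2 × Φ⁻¹(0.85) = 1.466, so d²/2 = 1.074.
- Calibrated prediction for score x at prevalence p: logit(p) + d·x − d²/2. Group B has ln 2 = 0.693 subtracted.
- Score at the cut-off: xc = [logit(t) − logit(p) + d²/2 + s] / d, with s = 0 in group A and s = 0.693 in group B.
- Sensitivity = 1 − Φ(xc − d).

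**Example, p = 24%, t = 20%**
- Group A: xc = (−1.386 + 1.153 + 1.074) / 1.466 = 0.57; sensitivity = Φ(0.89) = 81.4%.
- Group B: xc = (0.841 + 0.693) / 1.466 = 1.05; sensitivity = Φ(0.42) = 66.3%.

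**CSPH sensitivity, group A → group B**

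| Cut-off | Prevalence 24% | Prevalence 47% |
|---|---|---|
| 10% | 92.6% → 83.5% | 98.4% → 95.3% |
| 20% | 81.4% → 66.3% | 94.5% → 86.9% |
| 30% | 70.0% → 52.1% | 89.0% → 77.5% |
| 50% | 47.9% → 29.9% | 74.2% → 57.1% |

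**AUROC.** In 400,000 simulated patients at 24% prevalence, AUROC was 0.8498 both before and after the shift, a difference of exactly 0. Whether the 5% is read as absolute or relative, the rule is met.

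**Size of the shift.** With predicted odds divided by 1.5, 2 and 3, sensitivity at the 20% cut-off falls from 81.4% to 73.1%, 66.3% and 55.7% at 24% prevalence, and from 94.5% to 90.7%, 86.9% and 80.2% at 47%.

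**What a calibration measure would show.** With halved odds, mean predicted risk in group B is 16.4% against 24% observed, an observed/expected ratio of 24 / 16.4 = 1.46. At 47% prevalence it is 47 / 36.3 = 1.29. In group A the ratio is 1 by construction.

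**Why sensitivity alone is not the replacement.** The group A figures come from a perfectly calibrated model. At the 20% cut-off its sensitivity is 81.4% at 24% prevalence and 94.5% at 47%, a difference of 13.1 points with no miscalibration at all.

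**The case against.** Several points on the other side have force.

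- **Other fairness measures are not excluded.** Outcomes speaks of metrics in the plural, and the analysis section introduces the AUROC gap as one inclusion. Calibration plots, decision curves and net reclassification stand in the same paragraph as the subgroup analyses, so one could read them as applying by subgroup. A full analysis plan may say so. This stands as a possibility, but the article still fixes what equitable means, on AUROC alone.
- **The thresholds are less settled than a reader might infer.** The document does not say that the two thresholds are locked, and Table 1 says they will be refined in phase 2. A common pair for all patients is the natural reading, since no subgroup-specific thresholds are described, but it is an inference.
- **AIH overlap and MASH are weak examples.** Interventions makes both of them model inputs, so the model can fit a group-level offset. The point matters more for demographic groups, which do not appear in the list of candidate predictors under AI Model Development and Validation.
- **Recalibration is foreseen.** That section allows updating if calibration is poor in prospective deployment, though not by subgroup.
- **The zero gap is a constructed case.** A reader might infer that any tool missing more CSPH in one subgroup will show no AUROC gap and be declared equitable. The documents do not support that. Real miscalibration may also disturb ranking, sample gaps vary by chance, and nowhere is deployment made conditional on the 5% mark.

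**Conclusion.** The point holds as a statement about the criterion. An AUROC gap within 5% is compatible with systematic under- or over-prediction in a subgroup, so equitable performance of a threshold-based tool does not follow from it. That part is a mathematical property and needs no assumption about size.

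The size is illustrative. With AUROC 0.85 in both groups, a common 20% cut-off and predicted odds halved in one group, CSPH sensitivity is lower by 15 percentage points at 24% prevalence and by 8 at 47%, with a true gap of 0. The loss is as small as 3 points at a 10% cut-off with 47% prevalence and as large as 18 points at a 50% cut-off with 24% prevalence. Its direction is the same at any common cut-off.

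This is a badly fixed definition of a secondary outcome, not a flaw in the primary analyses.

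**What to change.** In the secondary outcome under Outcomes and in the third-aim part of Statistical Analysis:

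1. Define fairness by subgroup calibration (observed/expected ratio or calibration intercept, with 95% CIs) together with the AUROC gap, for the demographic and clinical subgroups already intended.
2. State that equitable performance will not be concluded from the AUROC gap alone.
3. Report sensitivity and specificity by subgroup at the final triage thresholds, with CIs, descriptively and beside subgroup prevalence. They should not serve as a pass mark, because they differ between groups with different prevalence even when the model is perfectly calibrated.

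The cost is a wording change and a few tabulations from predictions and outcomes that will be collected anyway; no extra patients or procedures are needed. The drawback is wide intervals in small subgroups, and hence a more cautious equity conclusion.

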### Sample Size and Power Considerations

Because this protocol involves model development, validation, and implementation feasibility, the planned sample size was based on expected cohort availability and anticipated outcome events rather than a conventional hypothesis-testing formula. The sample size determination for this study is primarily driven by the second aim, which focuses on validating the predictive model for CSPH. On the basis of preliminary data and published estimates, we anticipate enrolling approximately 600 patients with PBC across participating sites [7]. This cohort size reflects the expected availability of retrospective and prospective data within the study time frame and ensures adequate representation of key subgroups, including patients with AIH overlap and MASH [19,20].

On the basis of prior PBC cohorts, the prevalence of portal hypertension or CSPH in hepatology referral populations has been reported to range from approximately 24% to 47% depending on disease stage and case mix [25,26]. With a projected sample of 600 participants, this corresponds to an estimated 144 to 282 CSPH events, which provides a sufficient number of outcome events to support model development and validation and evaluate improvements in model discrimination relative to established criteria such as Baveno VII.

In addition, sample size considerations accounted for model complexity. Current methodological guidance for prediction modeling recommends ensuring an adequate number of outcome events relative to the number of predictor parameters to reduce the risk of model overfitting. The anticipated event counts in this cohort are expected to support the planned set of candidate predictors while maintaining an appropriate events-per-predictor ratio for stable model estimation [27].

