### AI Model Development and Validation

The predictive model will be developed using a prespecified machine learning pipeline. Candidate predictors will include longitudinal biochemical markers, platelet count, LSM, SSM, symptom scores, treatment response status, and relevant comorbidities. Features will be selected based on clinical relevance, data availability, and model stability, with highly collinear or sparsely available variables excluded or combined where appropriate.

The dataset will be divided into training, internal validation, and held-out testing subsets at the patient level to avoid data leakage. Model development will use gradient-boosted ensemble algorithms, with hyperparameters tuned within the training set using cross-validation. External validation will be performed using data from at least one participating site not used during model training where feasible.

Class imbalance will be addressed using strategies applied only within the training data, including class weighting or resampling approaches as appropriate. SHAP values will be generated to provide both patient- and cohort-level feature contributions. Model updating will not be performed during initial validation; if performance drift or poor calibration is observed during prospective deployment, recalibration or updating will be conducted using prespecified procedures and reported transparently.

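### The 5% AUROC parity gap that defines fairness is too narrow, against its sampling error at about 600 patients, to separate fair from unfair models

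*Protocol article*

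**What the plan says.** The Outcomes section of the protocol article lists, as a secondary outcome, "fairness metrics to ensure equitable model performance across demographic and clinical subgroups", and gives it a number: "defined as an AUROC parity gap of no more than 5" per cent. The Statistical Analysis section returns to it under the third aim: "Fairness metrics, including AUROC parity gaps across demographic and clinical subgroups, will be calculated to ensure equitable performance of the CDS tool". Neither place attaches an interval, a test or a minimum event count to the gap, or says whether 5% is absolute or relative. In the same paragraph of Statistical Analysis, intervals are promised for another outcome: "Feasibility indicators, such as recruitment and completion rates, will be reported as proportions with CIs".

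On size, Sample Size and Power Considerations states that "we anticipate enrolling approximately 600 patients with PBC across participating sites". Prevalence of CSPH "has been reported to range from approximately 24% to 47% depending on disease stage and case mix", and "this corresponds to an estimated 144 to 282 CSPH events". That section names AIH overlap and MASH as key subgroups but gives no share for either. On evaluation data, AI Model Development and Validation says: "The dataset will be divided into training, internal validation, and held-out testing subsets at the patient level to avoid data leakage". The test fraction is not given, and no section says which dataset the parity gap comes from. The Results section expects an AUROC of at least 0.85.

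**The concern.** A numeric limit on an observed difference is useful only if the difference can be measured more finely than the limit. A subgroup AUROC depends on the number of events and non-events in that subgroup, and a subgroup holding a tenth or a fifth of this cohort has few events. If the limit is smaller than the sampling error, a model that performs equally in all groups will often appear to breach it, and one that performs worse in a group will sometimes appear to meet it.

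The published statement about equity would then depend largely on chance. It could reassure wrongly about a subgroup or condemn a fair model. The tool is meant for a pilot in live clinics, and the abstract's conclusion refers to equitable care, so readers are likely to rely on the statement.

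**Working it through.** **The plan's own figure.** 600 × 0.24 = 144 and 600 × 0.47 = 282. Both stated event counts are reproduced exactly. The article gives no precision or power for the fairness criterion, so there is no fairness figure to reproduce.

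**Inputs from the article.** N about 600, prevalence 24% to 47%, AUROC 0.85, margin 5% read as 0.05 absolute.

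**Assumptions.** A subgroup share of 10% or 20%. An evaluation set of 120 (20% split), 180 (30% split) or all 600 as the best case.

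**Formulas.** The Hanley–McNeil variance of an AUROC A with m events and n non-events is

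V = [A(1−A) + (m−1)(Q1−A²) + (n−1)(Q2−A²)] / (mn), with Q1 = A/(2−A) and Q2 = 2A²/(1+A).

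The SE of the gap is √(V_subgroup + V_rest). The chance that a fair model exceeds the margin is 2[1 − Φ(0.05/SE)].

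**One cell in full: all 600, 10% subgroup, prevalence 24%.** With A = 0.85, A² = 0.7225, Q1 = 0.7391 and Q2 = 0.7811.

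- Subgroup: m = 14.4, n = 45.6. V = [0.1275 + 13.4 × 0.0166 + 44.6 × 0.0586] / 656.6 = 0.0045.
- Rest: m = 129.6, n = 410.4. V = 0.0005.
- SE = √0.0050 = 0.071. 0.05/0.071 = 0.71, so the chance of exceeding 0.05 is 48%.

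**All cells, true gap 0** (first value at 24% prevalence, second at 47%):

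| Evaluation set | Subgroup share | Subgroup events | SE of gap | 95% half-width | Fair model exceeds 0.05 |
|---|---|---|---|---|---|
| 600 | 10% | 14.4; 28.2 | 0.071; 0.054 | 0.139; 0.106 | 48%; 36% |
| 600 | 20% | 28.8; 56.4 | 0.053; 0.041 | 0.104; 0.079 | 34%; 22% |
| 180 | 10% | 4.3; 8.5 | 0.132; 0.101 | 0.258; 0.199 | 70%; 62% |
| 180 | 20% | 8.6; 16.9 | 0.097; 0.075 | 0.191; 0.147 | 61%; 50% |
| 120 | 10% | 2.9; 5.6 | 0.163; 0.126 | 0.320; 0.247 | 76%; 69% |
| 120 | 20% | 5.8; 11.3 | 0.120; 0.092 | 0.235; 0.181 | 68%; 59% |

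Simulation from binormal scores gives somewhat lower figures, because the closed form is a little conservative here: 58–74% on 120, 49–68% on 180 and 20–42% on all 600. I use the simulated ranges for the conclusion.

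**Several subgroups.** For two comparisons (10% and 20%), treated as independent, the chance that a fair model exceeds 0.05 at least once is 1 − (1−f₁)(1−f₂), with f₁ and f₂ from the table. On all 600 at 24% prevalence this is 1 − 0.52 × 0.66 = 66%. Over both prevalences it is 50–66% on all 600, 81–88% on 180 and 87–92% on 120. These use the closed form, so they lean high.

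**True gap of 0.10** (0.75 against 0.85). The chance of passing is Φ((0.05−0.10)/SE) − Φ((−0.05−0.10)/SE), with the subgroup variance taken at 0.75. For one 10–20% subgroup, simulation puts it at about 15–25% on all 600 and up to about 27% on a held-out set.

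**Sensitivity.**
- At AUROC 0.90, a fair model exceeds 0.05 for a single 10–20% subgroup in 13–40% on all 600 and 42–72% on a held-out set (closed form).
- Read as relative, 5% of 0.85 is 0.0425, which makes exceedance more likely still.
- With an even split of all 600, the simulated SD of the gap is 0.031–0.035, so the 95% half-width is 1.96 × 0.031 = 0.061 to 1.96 × 0.035 = 0.069. Even there a CI cannot fit inside ±0.05.

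**The case against.** The strongest reply is that much of this concerns what the article leaves unsaid. The CI method, the list of subgroups and minimum event counts commonly sit in an analysis plan, which is not shown. Their absence is not an error. The article also does not say that the gap will be judged without an interval, or on which dataset. That stands, and the point does not rest on it. It rests on the number that the article fixes as the definition of equity, which would remain the published line if an analysis plan added an interval.

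A reader might also infer that a fair model would usually fail at the planned subgroup sizes. The article does not support that. It states no subgroup sizes and no test fraction, so every probability above is conditional on assumed values. A single 10–20% subgroup judged on all 600 exceeds 0.05 in a minority of cases (20–42%). Exceedance is the more likely result for 10% subgroups on held-out sets of 120 or 180 and for 20% subgroups on 120. It is about even or somewhat above for 20% subgroups on 180. It also becomes likely when several subgroups are judged together.

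Finally, this is a secondary outcome, and nothing in the article makes the pilot or deployment depend on meeting 5%. That limits the consequence. It does not make the definition workable.

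**Conclusion.** The concern holds in this form: as a definition of equitable performance, a 5% gap cannot separate fair from unfair models at about 600 patients. For subgroups of 10–20%, the standard error of the gap is close to 0.05 on the whole cohort and well above it on a held-out set of 120 or 180. A fair model breaches the limit in 20–42% of single comparisons at best and 58–74% on 120 held-out patients. A true gap of 0.10 meets it in about 15–27%.

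These figures assume AUROC 0.85, prevalence of 24–47%, the stated shares and evaluation sets, and an absolute margin judged on the observed gap. The conclusion does not hang on one choice. An AUROC of 0.90 lowers the rates but leaves them substantial, and a relative margin raises them. The primary outcomes are not affected.

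**What to change.** In Outcomes and Statistical Analysis:

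- Report each subgroup AUROC gap with a bootstrap 95% CI and the subgroup's event count.
- State that 5% means 0.05 absolute, and use it as a descriptive benchmark, not as the definition of equity.
- Call a disparity shown only when the CI lies wholly beyond 0.05. Call parity shown only when the CI lies within ±0.05. Report anything else as inconclusive.
- Replace *ensure* with *estimate* in both sections.

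Keep the held-out evaluation. Out-of-fold estimates on all patients could be added as a supplementary analysis, with tuning nested within folds. They should not replace the held-out test, because they come from several fitted models and not from the one to be deployed.

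The cost is wording and a bootstrap, and the article says recruitment has not begun. The real downside is that almost no subgroup, large or small, could be declared equivalent within 0.05. A 95% half-width of 0.05 would need an evaluation set of about 970 to 1,640 patients for an even split and 1,510 to 2,560 for a 20% subgroup (47% and 24% prevalence, AUROC 0.85). The study would give estimates of the gaps, not a fairness verdict, and the article should say so.
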